### **7.3 Efficacy Assessments**

All enrolled patients will undergo follow-up MRI or CT at 24 hours after treatment. Clinical assessments will be at baseline and 24 hours (NIHSS), as well as day 90 modified Rankin Scale (mRS, EQ5D and PROMIS10). The 24 hour NIHSS will be measured by an observer blind to treatment allocation and not involved in the patient's baseline assessment or clinical care. Day 90 and day 360 mRS, EQ5D and PROMIS10 will be performed centrally by a trained assessor via telephone (who is blinded to treatment).

### **7.4 Study Restrictions**

- Dietary - Not Applicable
- Smoking – Not Applicable
- Confinement - Not eligible
- Position / Ambulation – patients to be on strict bed rest for 24 hours following administration of trial medications.
- Concomitant Medication – patients not to receive any anti-coagulant/ anti-platelet medications in the first 24 hours following administration of trial medication
- Other Restrictions - Nil

## **8. Investigational products**

For more detail on tenecteplase See Appendix 1.

### **8.1 Comparator Justification**

The ETERNAL LVO study seeks to investigate the clinical benefit of tenecteplase therapy in addition to thrombectomy compared to standard of care. Alteplase is the standard of care treatment for acute ischaemic stroke patients presenting within 4.5 hours of symptom onset. However, in the extended time window, there is not strong evidence for use of IV thrombolysis. In LVO patients, our recent EXTEND study showed only a 3% absolute increase in mRS 0-1 at 3 months with alteplase compared to placebo (unadjusted). Following our EXTEND results we expect there will be some variation in the standard of care for such patients with target mismatch in the late time window and anticipate that some clinicians will now wish to give alteplase. However, given that the EXTEND results, as a single trial, may not be sufficient to generate a strong guideline recommendation regarding administration of thrombolysis beyond 4.5 hours, we expect variation in clinical

practice in terms of whether ‘standard of care’ for LVO patients beyond 4.5 hours includes IV alteplase or no thrombolytic. To accommodate this expected variation in practice the ‘standard of care arm’ will allow either 0.9mg/kg alteplase or no lytic at the local investigator’s discretion, but with the control group treatment pre-specified by the investigator (i.e. alteplase or not) prior to randomisation (covariate adjusted randomisation to minimise imbalances in key prognostic covariates between treatment groups. For example, investigators may be more likely to choose no lytic in patients with larger ischemic core volumes (due to perceived risk of ICH), or in those treated later in the 24 hour time window. If not adjusted for at randomisation, this might lead to an imbalance for these variables between the tenecteplase and ‘standard of care’ groups.

## **8.2 Description of Investigational Product**

The investigational product tenecteplase (Metalyse™, Boehringer Ingelheim) is a genetically modified form of alteplase. Within this study, tenecteplase lyophilised powder will be reconstituted in a glass vial with water for injection at concentration 5mg/mL (e.g. 40mg tenecteplase in 8mL water). Vials should be maintained at a temperature less than 30°C and protected from light as per the manufacturer’s product information. Investigational use of Tenecteplase in this study will be managed under the applicable Regulatory mechanism for each participating country. Off the shelf tenecteplase will be used in this study. Staff will be trained in the mixing and administration of the drug.

## **8.3 Administration**

After reconstitution of the investigational product, a dedicated IV cannula should be used for administration. The dose of tenecteplase to be administered is given as a bolus over approximately 5 seconds. The investigational product should be used immediately after reconstitution. No other anticoagulants or antiplatelet agents are to be given within 24 hours of administration of the investigational product.

## **8.4 Randomisation**

Patients will be randomized according to a centralised web-based procedure coordinated via the Melbourne Brain Centre.

The randomization system will be based on computer generated randomization code lists, using a covariate-adjusted randomisation procedure to minimise imbalances on the following covariates: clinician intention to give alteplase or no thrombolysis if randomised to standard of care, age, NIHSS, premorbid mRS, site of Large Vessel Occlusion (Intracranial ICA and M1 vs extracranial ICA and M2, with tandem ICA occlusions to be considered intracranial for the purpose of covariate adjustment) and onset-to-randomization time (0-4.5, 4.5-12 and 12-24 hours, where wake-up stroke/uncertain onset is ‘last seen well within last 24 hours’).

## **8.5 Blinding/Unblinding**

The investigational treatment is open-label. All those involved in the subsequent clinical and imaging assessment of outcomes will be blinded to treatment allocation. The Data Safety Monitoring Board (DSMB) will have access to unblinded grouped data.

## **8.6 Product Labelling**

Commercial packages of tenecteplase (Metalyse™, Boehringer Ingelheim) are labelled by the manufacturer, Boehringer Ingelheim, with storage conditions (store below 30°C), batch number and expiry date. Commercial packages of tenecteplase (Metalyse™, Boehringer Ingelheim) will be used for the Investigational product for this study and be provided by each participating Site under the applicable Regulatory mechanism. Commercial packages are labelled by the manufacturer, Boehringer Ingelheim, with storage conditions (store below 30°C), batch number and expiry date.

## **8.7 Handling and Storage of Investigational Product**

Investigational product will be stored below 30°C until use in accordance with manufacturer's instructions. The investigator or his/her designee must maintain an adequate record regarding the administration of all investigational product within the trial. If standard hospital supplies are being used then temperature monitoring is not required. Do not use beyond the expiration date stamped on the vial. Drug name, dose, route, batch and expiry should all be documented in the patient's drug chart or other applicable source documents to enable source data verification of the randomized treatment and availability of all information required for Safety reporting purposes.

The investigator must agree to use the investigational product only in accordance with the protocol.

# **9. Adverse events and serious adverse events**

The investigator is responsible for the detection and documentation of events meeting the criteria and definition of an adverse event (AE) or a serious adverse event (SAE) as provided in this protocol. During the study, when there is a safety evaluation, the investigator or site staff will be responsible for detecting AEs and SAEs, as detailed in this section of the protocol

## **9.1 Definition of an Adverse Event (AE)**

Any untoward medical occurrence in a patient or clinical investigation subject, temporarily associated with the use of a medicinal product, whether or not considered related to the medicinal product.

*An AE can therefore be any unfavourable and unintended sign (including an abnormal laboratory finding), symptom, or disease (new or exacerbated) temporally associated with the use of a medicinal product,*

Protocol Number: UOM2102

Protocol Title: ETERNAL LVO

*whether or not considered related to the medicinal product. For marketed medicinal products, this also includes failure to produce benefits (i.e. lack of efficacy), abuse or misuse.*

Examples of an AE **include**:

- Exacerbation of a chronic or intermittent pre-existing condition including either an increase in frequency and/or intensity of the condition.
- New conditions detected or diagnosed after investigational product administration even though it may have been present prior to the start of the study.
- Signs, symptoms, or the clinical sequelae of a suspected interaction.
- Signs, symptoms, or the clinical sequelae of a suspected overdose of either investigational product or a concurrent medication (overdose per se should not be reported as an AE/SAE).

Examples of an AE **do not include** a/an:

- Medical or surgical procedure (e.g. endoscopy, appendectomy); the condition that leads to the procedure is an AE.
- Situations where an untoward medical occurrence did not occur (social and/or convenience admission to hospital).

In this study, AEs may include pre- or post-treatment events that occur as a result of protocol-mandated procedures (i.e. invasive procedures, modification of subjects' previous therapeutic regimen).

## **9.2 Definition of a Serious Adverse Event (SAE)**

A serious adverse event is any untoward medical occurrence that, at any dose:

a) Results in death,

b) is life-threatening,

*Note: The term 'life-threatening' in the definition of 'serious' refers to an event in which the subject was at risk of death at the time of the event. It does not refer to an event, which hypothetically might have caused death if it were more severe.*

c) requires hospitalisation or prolongation of an existing hospitalisation,

*Note: In general, hospitalisation signifies that the subject has been detained (usually involving at least an overnight stay) at the hospital or emergency ward for observation and/or treatment that would not have been appropriate in the physician's office or out-patient setting. Complications that occur during hospitalisation are AEs. If a complication prolongs hospitalisation or fulfils any other serious criteria, the*

Protocol Number: UOM2102

Protocol Title: ETERNAL LVO

*event is serious. When in doubt as to whether 'hospitalisation' occurred or was necessary, the AE should be considered serious.*

*Hospitalisation for elective treatment of a pre-existing condition that did not worsen from baseline is not considered an AE.*

d) Results in disability/incapacity, or

*Note: The term disability means a substantial disruption of a person's ability to conduct normal life functions. This definition is not intended to include experiences of relatively minor medical significance such as uncomplicated headache, nausea, vomiting, diarrhoea, influenza, and accidental trauma (e.g. sprained ankle) which may interfere or prevent everyday life functions, but do not constitute a substantial disruption.*

e) Is a congenital abnormality / birth defect.

Medical and scientific judgement should be exercised in deciding whether reporting is appropriate in other situations, such as important medical events that may not be immediately life-threatening or result in death or hospitalisation, but may jeopardise the subject or may require medical or surgical intervention to prevent one of the other outcomes listed in the above definition. These should also be considered serious. Examples of such events are invasive or malignant cancers, intensive treatment in an emergency room or at home for allergic bronchospasm, blood dyscrasias or convulsions that do not result in hospitalisation, or development of drug dependency or abuse.

### **9.3 Clinical Laboratory Abnormalities and Other Abnormal Assessments as AEs and SAEs**

Abnormal laboratory findings (e.g. clinical chemistry, haematology, urinalysis) or other abnormal assessments (e.g. ECG, vital signs) that are judged by the investigator as clinically significant will be recorded as AEs or SAEs if they meet the definition of an AE, as defined in Section 9.1 or SAE as defined in Section 9.2. Clinically significant abnormal laboratory findings or other abnormal assessments that are detected during the study or are present at baseline and significantly worsen following the start of the study will be reported as AEs or SAEs. However, clinically significant abnormal laboratory findings or other abnormal assessments that are associated with a disease reported in the medical history, unless judged by the investigator as more severe than expected for the subject's condition, or that are present or detected at the start of the study and do not worsen, will not be reported as AEs or SAEs.

The investigator will exercise his or her medical and scientific judgement in deciding whether an abnormal laboratory finding or other abnormal assessment is clinically significant.

#### **9.4 Time Period, Frequency, and Method of Detecting AEs and SAEs**

All adverse events will be recorded between the time of consent and discharge or Day 7 (whichever occurs first) post study drug administration. Serious adverse events will continue to be recorded until 90 days post study drug administration. Each subject will be monitored regularly by the investigator and study personnel for adverse events occurring during the first 24 hours post study drug administration. During the in-clinic treatment period, the investigator or designee will enquire about AEs by asking the following non-leading questions:

During the initial AE enquiry subjects should be asked:

*“How are you feeling?”*

At subsequent interviews subjects should be asked:

*“Since you were last asked, have you felt unwell or different from usual?”*

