## 7. Study assessments and Procedures

### 7.1 Screening

Baseline physical examination will be performed on potentially eligible patients.

Multi-modal CT or MRI will be performed to assess eligibility for acute thrombolytic and thrombectomy treatment including perfusion imaging analysed with MiStar as part of standard care for stroke patients. It is expected the majority of patients will be recruited using CT.

Neurological impairment and functional scores (NIHSS, pre-stroke mRS) will be assessed by a neurologist or trained health care professional.

Bloods for standard care diagnostic evaluations will be collected and analysed.

Patients will be assessed for trial eligibility according to the Inclusion/Exclusion criteria including processing of the imaging data to assess for vessel occlusion and mismatch.

Informed consent will be obtained from patients or their authorised representative according to the Independent Ethics Committee (IEC) approved patient information and informed consent procedure and documentation which may include consent to continue participation after initial “emergency treatment to prevent serious damage to the patient’s health” in some jurisdictions.

**Imaging:** Centres will process the CT or MR images using MiStar to determine eligibility. Patients will have standardised multimodal CT or MR prior to treatment.

**Medical history, concomitant medications & ECG:** Details of patients’ medical history (including stroke history) and concomitant medications will be recorded. Results of ECG performed as part of standard care will be recorded if available.

**Blood and urine collection:** Results from standard care blood tests performed at screening will be recorded (routine haematology, biochemistry and coagulation screening tests as described in Appendix 1. Study schedule).

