## 7.2 Study Procedures

### 7.2.1 Day 0 – Treatment

**Intravenous thrombolytic treatment:** Patients will receive open-label intravenous tenecteplase at a dose of 0.25 mg/kg, given as a bolus or ‘standard of care’, which will include intravenous alteplase at the standard dose of 0.9 mg/kg up to a maximum of 90mg (10% as bolus and the remainder over 1 hour), or no thrombolytic. Randomisation will be performed as described above. The time of bolus and infusion commencement will be recorded.

Close neurological observation will be conducted primarily during the first 48 hours after treatment administration according to local clinical practice.

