### **15.4 Informed Consent**

As treatment efficacy in acute ischemic stroke is strongly time dependent it is critical that trial procedures do not unduly delay initiation of standard therapy. Existing data on tenecteplase indicate that it is very unlikely to be less effective or higher risk than alteplase. To minimize delay in “door-to-needle” we will request HREC approval to use the section 42A clause in the Victorian Guardianship and Administration Act that emergency treatment that is necessary to prevent serious injury to the patient’s health may be commenced without consent and the analogous provisions in the updated Victorian Medical Treatment Planning and Decisions Act 2016. We will then undertake standard written consent to continue follow-up in the trial. For jurisdictions that do not permit this approach we will use an abbreviated 1-page patient information form as used in the TASTE randomized trial of tenecteplase vs alteplase (ACTRN12613000243718). Each participant (or authorised representative where this is applicable) will be given a full explanation of the nature and purposes of the study, and a copy of the Patient Information Sheet to review. Once the essential study information has been provided, and the Investigator is assured that each patient or their representative understands the implications of participating or continuing in the study as appropriate, the subjects or their representatives will be asked to give consent to the study by signing the informed consent form. The consent forms shall be signed and dated by the appropriate parties.

A notation of the nature of consent will be made on the subject’s medical history/patient notes, and recorded in the eCRF. The completed consent forms will be retained by the Investigator and a copy of these will be provided by the Investigator to the subject.

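### Section 9.4 opens adverse event recording at consent although 7.1 and 15.4 allow treatment before consent in some jurisdictions, and its Day 7 and 90-day clocks have no start for controls given no thrombolytic

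*Protocol*

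**What the plan says.** Section 9.4 gives the recording rule: "All adverse events will be recorded between the time of consent and discharge or Day 7 (whichever occurs first) post study drug administration". For serious events it adds only a later end: "Serious adverse events will continue to be recorded until 90 days post study drug administration". The same paragraph also has each subject monitored for adverse events over the first 24 hours after the study drug.

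Section 15.4 says that approval will be sought to rely on Victorian law under which emergency treatment to protect the patient's "health may be commenced without consent and the analogous provisions in the updated Victorian Medical Treatment Planning and Decisions Act 2016". The order of events follows: "We will then undertake standard written consent to continue follow-up in the trial". Other places get a different route: "For jurisdictions that do not permit this approach we will use an abbreviated 1-page patient information form". Section 7.1 agrees. It refers to an approved consent procedure "which may include consent to continue participation after initial" emergency treatment, in some jurisdictions.

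Section 7.2.1 describes the control arm as alteplase "or no thrombolytic. Randomisation will be performed as described above". Some controls therefore never receive a thrombolytic.

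**The concern.** A safety recording window should start at the same defined moment for every randomised patient, no later than first exposure. Here the start is an administrative event that, on one permitted route, comes after treatment. Followed to the letter, the rule leaves out whatever happens between treatment and consent. Whether an early event is recorded could then depend on the consent law of the jurisdiction, in a trial planned for 50 to 75 centres in many countries (section 6). The recorded events also feed the causality and expedited-reporting steps in 9.7 and 9.8.

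The end of the window has a related weakness. It is counted from a drug administration that part of the control arm does not have, in an open-label trial where both arms need the same time zero.

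**Working it through.** No sample size, power or rate is involved, so the check is a comparison of the sections.

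**1. Start of the window.** Section 9.4 names consent. It gives serious events no other start, so by default they share it.

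**2. Order of consent and treatment.** There are three cases:
- Consent before treatment (for example with the abbreviated form in 15.4): the window opens before exposure and the gap is zero.
- Consent after emergency treatment (7.1, 15.4): gap = time of consent minus time of treatment. The protocol sets no upper limit on this interval.
- No consent ever obtained, including death before consent: the window as written never opens. The current exclusion list in 6.2 does not require that consent be obtainable, so such patients can be enrolled.

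**3. Does other text move the start back?**
- The 24-hour sentence in 9.4 runs from the study drug and covers every subject. It describes monitoring and leaves the recording start unchanged.
- Section 7.2.2 has all patients asked about adverse events at 24 ± 6 hours after treatment, that is at 18 to 30 hours. If consent comes later than that, the enquiry itself precedes the opening of the recording window.
- Section 9.6 requires prompt SAE notification for any study subject, and 9.5 requires review of hospital notes once an event occurs. Neither names a start date.
- Section 9.10 classes events outside the 9.4 period as post-study. Its release from active searching concerns former participants, so it neither waives nor supplies a rule for an inpatient awaiting consent.
- The schedule of events shows consent only at screening, which does not fit the deferred route. It marks adverse events at Day 1 and Day 90, with no entry at Day 0.

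These passages suggest that capture from treatment was intended. None of them amends the stated start.

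**4. Which outcomes depend on the window?** In 12.2, sICH is timed within 36 hours of treatment, and death from any cause and mRS 5-6 at 3 months are separate outcomes. In 12.4, the DSMC parameters are mortality at three months and sICH within 36 hours of intervention. None refers to the 9.4 window. What remains exposed is early AEs and SAEs outside these endpoints, such as bleeding that does not meet the sICH definition, or allergic reactions.

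**5. End of the window.** Non-serious events stop at the earlier of discharge and Day 7 after the drug. For a control given no thrombolytic, discharge still applies but Day 7 has no origin. The 90-day SAE limit has no origin either. The synopsis already times the 24-hour imaging and NIHSS from randomisation, so a clock common to both arms is in use elsewhere in the protocol.

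**The case against.** The best reply is that the protocol, read as a whole, already captures these events. It requires monitoring for 24 hours after the drug, asks every patient at Day 1, requires upload of additional in-hospital imaging, and has any SAE notified promptly. A sensible site would record an early bleed whatever the date on the consent form. The deferred route is also conditional on ethics approval and on jurisdiction. Much of this stands: the defect is a conflict between rules, not proof that data will be lost.

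Four stronger readings are tempting, and the document does not support them:
- A reader might infer that the main safety comparison understates harm. It does not follow, because sICH, death and mRS 5-6 are defined without reference to the window.
- A reader might infer that most patients lose many hours of capture. The protocol states neither the share under deferred consent nor the delay, and the gap is zero for those who consent first.
- A reader might infer a bias between arms. The consent route follows jurisdiction, not allocation, so both arms at a site face the same start rule.
- A reader might infer that controls given no thrombolytic have no end to their window. Discharge still closes the AE window, and the schedule has a Day 90 entry. Only the origin of the Day 7 and 90-day counts is undefined.

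What survives is that a site following 9.4 literally may leave out pre-consent events, and that no other section overrides it.

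**Conclusion.** The point holds as an internal conflict that should be corrected. Section 9.4 ties the start of AE and, by default, SAE recording to consent, while 7.1 and 15.4 allow consent to follow treatment. For deferred-consent patients the literal window misses the interval from treatment to consent. For patients who die before consent or never give it, it misses everything.

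The size cannot be given, because the protocol states neither the proportion affected nor the delay. The effect is limited to AEs and SAEs outside the named safety endpoints, and to sites that apply 9.4 as written despite the monitoring and Day 1 provisions. The undefined origin of the Day 7 and 90-day counts is a second, smaller defect, confined to controls given no thrombolytic.

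The conclusion assumes that the deferred route is approved in at least one jurisdiction. If it is not, only the second defect remains.

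**What to change.** In 9.4, record adverse events from randomisation, whatever the consent route, to discharge or Day 7 after randomisation, whichever comes first. Record serious adverse events from randomisation to Day 90 after randomisation. Apply both rules identically in the two arms.

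State that events before consent are included, as are events in patients who die before consent, as far as the ethics approval allows. Say how patients for whom consent is never obtained are handled. Align 15.4, and amend the schedule of events so that it shows the deferred-consent route and an adverse event entry at Day 0.

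The cost is a few sentences, CRF guidance and the usual ethics review of an amendment. Design, sample size and treatment are unaffected.
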